**Statistical analysis:**

Sample size was calculated to achieve 90% power at an alpha of 0.025 to detect a non-inferiority margin of ≤ 1 cm on the VAS, using a one-sided, two-sample t-test. Baseline demographic and clinical characteristics will be analysed for comparability between groups. Differences in primary (VAS pain score) and secondary outcomes between groups will be analysed by intention to treat and per protocol analysis using Student's t-test and ANOVA.

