#### Primary outcome

Decrease in pain measured by VAS at 30 minutes post-intervention.

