### Sample size

A sample size of 133 in each group will be required to achieve 90% power to detect non-inferiority using a one-sided, two-sample t-test. The significance (alpha) of the test is 0.025. The non-inferiority margin is ≤ 1 cm on the VAS and the true difference between the means is assumed to be zero (cms). A standard deviation (SD) of ± 2.5 on the VAS was conservatively estimated from results reported in a recent meta-analysis [6] of SWI studies. As consent and randomisation will occur in the birth suite, attrition is expected to be minimal. However, we have estimated a 20% attrition to account for cases of precipitate birth prior to the assessment of the primary outcome, or other unforseen reasons for withdrawal such as emergency caesarean section. Thus a total of 319 participants will be required.

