### Statistical analysis

Demographic and other baseline characteristics will be analysed for comparability between groups to assess the adequacy of randomisation. Differences in VAS pain score between the two groups will be analysed using Student's t-test and analysis of variance (non-parametric tests used if data is highly clustered toward extremes). Data analysis for the primary outcome will determine if the treatment effect lies within the a priori defined non-inferiority margin (± 1 cm) and the null effect (0 cm) at a one-sided alpha of 0.025. The pre-specified non-inferiority margin was based on a one cm (95% CI 0.6-1.4 cm) minimally clinically significant difference reported for VAS in severe pain [14]. The Mann-Whitney U test will be utilised for non-parametric data and chi-squared test for categorical variables. Women who give birth or elect for narcotic and/or regional analgesia after the collection of the primary measure (VAS score 30 minutes post injection) but before the completion of the secondary outcomes (VAS up to 120 mins) will be included in the trial. Women giving birth or electing for narcotic and/or regional anaesthesia prior to the collection of the primary outcome measure will be included in the Intention to Treat (ITT) analysis. The conservative nature of ITT may obscure differences between treatments groups therefore increasing the chance of falsely declaring equivalence [19]. To address this, some authors have recommended that Per Protocol (PP) analysis also be conducted alongside ITT to provide a more robust conclusion if both methods support the non-inferiority [9,20]. Other authors [21] argue that the benefits of ITT analysis continue to outweigh the PP approach. As it is unlikely that participants in this trial will cross from one intervention to another, the ITT approach will be used unless the dropout out rate exceeds the estimated margin allowed of 20%. Should the dropout rate exceed 20% then a PP analysis will also be conducted. Figure 4 outlines possible scenarios for the outcome of the data analysis based on the pre-defined noninferiority margin, indicated as the shaded area. Error bars indicate 90% confidence intervals (CI). If the CI is completely to the left of zero, the treatment is inferior (scenario A). Scenarios C,D and E indicate noninferiority as the CI lies within the specified margin (shaded area). Scenario F would indicate superiority. An inconclusive result (scenario B) is unlikely as the sample size is sufficiently powered to provide a result [22].

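### Early births and early rescue analgesia enter the ITT primary analysis with no condition on the 30-minute score, so relief they bring may be credited to the injection

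*Protocol article*

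**What the plan says.** All references are to the protocol article.

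- **Primary outcome**: "Decrease in pain measured by VAS at 30 minutes post-intervention". No condition is attached about what happens between injection and score.
- **Statistical analysis**, on events before that score: "Women giving birth or electing for narcotic and/or regional anaesthesia prior to the collection of the primary outcome measure will be included" in the ITT analysis. The value these women contribute is not given.
- **Sample size**, on the same kind of event: "we have estimated a 20% attrition to account for cases of precipitate birth prior to the assessment of the primary outcome". Emergency caesarean is named there as another reason for withdrawal.
- **Statistical analysis**, on the second analysis set: "Should the dropout rate exceed 20% then a PP analysis will also be conducted". Below that rate ITT stands alone. The same paragraph acknowledges that ITT can hide differences and so raise the risk of a false finding of equivalence.
- **Abstract**, Statistical analysis: outcomes "will be analysed by intention to treat and per protocol analysis using Student's t-test and ANOVA", with no dropout condition.

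**The concern.** Entry requires a back pain VAS of at least 7. If birth or an effective block brings the 30-minute VAS near zero, the recorded fall is about 7 cm, and an analysis of observed scores attributes all of it to the injection. A woman who turns to an epidural because the injection failed could then rank among its best responders.

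In a superiority trial such contamination mostly costs power. In a non-inferiority trial, shrinking the difference between arms moves the result toward the claim the trial hopes to make. If early rescue is commoner after the single injection because it works less well, its failures improve its mean.

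Per-protocol analysis, the safeguard the article itself discusses, may never run. The reason given for relying on ITT is that women are unlikely to cross between techniques, which does not address birth or other analgesia. Women retained in ITT may also not count as dropouts, so these events need not trigger it.

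**Working it through.** **The plan's own figure.** Inputs (Sample size): margin 1 cm, SD 2.5 cm, true difference 0, one-sided alpha 0.025, power 90%. Normal approximation: n = 2 × (1.960 + 1.282)² × 2.5² / 1² = 131.3, so 132 per arm. The noncentral t gives 89.9% power at 132 and 90.1% at 133, so 133 per arm reproduces. The total reproduces as 266 × 1.2 = 319.2, or about 159 randomised per arm.

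**Illustration if observed scores are used.** The article gives no early event rates and no post-event scores, so these are assumptions:

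- mean fall without an event: 4 cm with four injections, 3 cm with one (a true deficit equal to the margin), SD 2.5;
- mean fall after an event: m = 5 to 7 cm, SD 1.5;
- event proportions p0 (four injections) and p1 (single); 159 per arm.

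Expected difference: d = [4(1 − p0) + m·p0] − [3(1 − p1) + m·p1] = 1 + p0(m − 4) − p1(m − 3).

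Probability of declaring non-inferiority: Φ((1 − d)/SE − 1.96), with SE from the mixture variances.

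| Single v four | d (cm) | False non-inferiority |
|---|---|---|
| 0% v 0% | 1.00 | 2.5% |
| 5% v 5% | 0.95 | 3.7% |
| 10% v 10% | 0.90 | 5.2-5.5% |
| 5% v 2% | 0.86-0.92 | 4.7-7.0% |
| 10% v 5% | 0.75-0.85 | 7.8-13% |

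Worked line, 10% v 5% with m = 7: d = 1 + 0.05 × 3 − 0.10 × 4 = 0.75; SE = 0.294; Φ(0.25/0.294 − 1.96) = Φ(−1.11) = 13%. With 133 per arm the 10% v 5% row becomes 7.1-11.8%.

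**Direction.** At equal rates d = 1 − p, whatever m is. The bias reverses when p0(m − 4) > p1(m − 3): for m = 7 when p0 exceeds 4/3 of p1, for m = 5 when p0 exceeds twice p1.

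**Upper case.** Suppose every rescued woman would have had no fall without rescue, and the true 1 cm deficit counts her as 0. Recording 7 cm instead gives bias 7 × (0.10 − 0.05) = 0.35 cm. With SE = 2.5 × √(2/133) = 0.307, Φ(0.35/0.307 − 1.96) = 20.7%.

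**If events are scored as no relief instead.** d = 4(1 − p0) − 3(1 − p1). For 5% v 2%, d = 1.07 and the rate is 1.4%; for 10% v 5%, d = 1.10 and 1.1%. At 10% in each arm d = 0.90 and the rate is 5.3%, so this scoring removes the credit for unequal rescue but not dilution at equal rates.

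**The case against.** A reader might infer that the protocol counts birth or an epidural as relief from the injection. It does not say so. It places these women in the ITT set and assigns no score, and the Sample size section suggests that women who give birth early may have none. Electing analgesia also does not mean that it has acted by 30 minutes. The effect described here is therefore conditional on observed scores being used.

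Further points on the other side:

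- *The two sections need not contradict each other.* A woman can belong to the ITT set and lack a score, and an attrition allowance concerns recruitment. This stands in part: it is not a flat contradiction, but the article leaves unsettled whether she contributes a score.
- *The scoring rule belongs in an analysis plan.* Fair for the imputation detail. But the article itself fixes inclusion, an unconditional outcome and a dropout trigger for per-protocol, and the abstract disagrees with that trigger. Those are stated choices.
- *Using the score whatever follows is a recognised ITT strategy.* True, which is why that analysis should stay. It compares policies of injection plus later care, while the Background aims to compare the analgesic benefit of the two techniques.
- *The rates are assumed.* True. Entry is limited to first-stage labour, and the article expects minimal attrition while allowing 20%. If early events are rare, the effect is small: 2% in each arm gives 2.9%.

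**Conclusion.** The concern holds in conditional form. As written, the plan allows relief from birth or effective rescue to enter the non-inferiority comparison as injection effect, and makes its safeguard depend on a dropout rate that these events may not affect.

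At a true 1 cm deficit the illustrative false non-inferiority rate is about 5% with 10% events in both arms and about 8-13% with 10% (single) v 5% (four), against 2.5% nominal. The 21% figure is an upper case that rests on a different definition of the true deficit and on a full 7 cm swing per rescued woman. All of these depend on assumed event rates and post-event scores.

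A reader might also infer that the bias always favours non-inferiority. The documents do not support that: it depends on the score used and on event rates by arm, and it can reverse. Leaving the value open also allows the choice to be made after the data are seen, so it should be settled before analysis.

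**What to change.** In the Statistical analysis section:

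1. Name one analysis in which a VAS taken after birth, or after narcotic or regional analgesia, is not credited to the injection. One option scores rescue as no relief and uses the last pre-birth score for births; other choices are defensible if fixed in advance.
2. Run it alongside the observed-score ITT analysis whatever the dropout rate, and claim non-inferiority only if both support it. Both are needed because no-relief scoring alone does not cure dilution at equal rates.
3. Report early births and early rescue by arm.
4. Reconcile the abstract, Sample size and Statistical analysis sections on whether per-protocol is conditional and whether women with early events count as attrition, as ITT members, or as ITT members without a score.

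Cost: mainly wording, plus a little data. The 10-minute VAS is already collected. The start time of analgesia is not listed in Data collection. Birth time and other analgesia are listed for Site One, and Site Two's database items are said to differ, so analgesia start time and birth time should be recorded at both sites. No-relief scoring may raise the SD, and requiring two analyses to agree makes the non-inferiority claim slightly harder to win.

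### The primary test is set at one-sided alpha 0.025 but the result is classified with 90% confidence intervals, a one-sided 0.05 rule, and the protocol does not say which governs

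*Protocol article*

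**What the plan says.** The error level is given in three places, and they agree.

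- The abstract ties the alpha to the planned numbers: "Sample size was calculated to achieve 90% power at an alpha of 0.025 to detect a non-inferiority margin of ≤ 1 cm on the VAS".
- The section on sample size gives 133 per group and 90% power for a one-sided t-test, and fixes the level: "The significance (alpha) of the test is 0.025".
- Statistical analysis: the primary outcome is judged against the margin "and the null effect (0 cm) at a one-sided alpha of 0.025".

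The Statistical analysis section then explains how a result will be classified, by reference to Figure 4. There, "Error bars indicate 90% confidence intervals (CI"), and the verdict follows from where the interval falls: "Scenarios C,D and E indicate noninferiority as the CI lies within the specified margin (shaded area"). The margin in this section is written as ±1 cm. In the Hypothesis section it is one-directional: the null is a difference of 1 cm or more and the alternative a difference below 1 cm.

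No 95% interval or 97.5% bound for the treatment difference is mentioned. The only 95% interval in the text is the 0.6 to 1.4 cm range around the minimal clinically significant difference.

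**The concern.** A one-sided test at 0.025 corresponds to one bound of a two-sided 95% interval. One bound of a two-sided 90% interval corresponds to a one-sided test at 0.05. The section therefore holds two decision rules with different error levels, and the same data can pass one and fail the other.

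What is at stake is the trial's main conclusion. The interval scheme is the only worked rule in the document for turning an estimate into inferior, non-inferior, superior or inconclusive, so an analyst could reasonably follow it. Because neither rule is given priority, the choice could also be made after the data are seen, and the 90% rule is always the more lenient on non-inferiority.

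**Working it through.** **Inputs.** From the Sample size section: margin 1 cm, true difference 0, SD 2.5 cm, 133 per group, one-sided alpha 0.025, power 90%. From the Statistical analysis section: 90% intervals in the classification scheme.

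**Step 1. Reproduce the plan's sample size.** The normal approximation is n per group = 2 × SD² × (z for alpha + z for power)² / margin².

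- At one-sided 0.025: 2 × 6.25 × (1.960 + 1.282)² / 1² = 131.4, so 132. The exact noncentral-t calculation gives 133, with power 90.1%.
- At one-sided 0.05: 2 × 6.25 × (1.645 + 1.282)² / 1² = 107.1, so 108. The exact calculation also gives 108.

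The stated 133 is therefore a one-sided 0.025 figure and does not come from 0.05.

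**Step 2. Error level of the interval rule.** For one bound it is (1 − confidence level)/2.

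- 90% interval: (1 − 0.90)/2 = 0.05.
- 95% interval: (1 − 0.95)/2 = 0.025.

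A simulation of 2,000,000 trials at a true deficit of 1 cm (SD 2.5, 133 per group) gave false non-inferiority of 0.0497 with the 90% interval and 0.0249 with the 95% interval. Requiring the interval to lie inside both +1 and −1 cm does not lower the 90% figure, which stays at 0.0497.

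**Step 3. Where the two rules disagree.** The standard error is 2.5 × √(2/133) = 0.307 cm, with 264 degrees of freedom.

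| Interval | Half-width (cm) | Largest observed deficit still non-inferior (cm) |
|---|---|---|
| 90% | 0.506 | 1 − 0.506 = 0.494 |
| 95% | 0.604 | 1 − 0.604 = 0.396 |

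An observed single-injection deficit between 0.396 and 0.494 cm is non-inferior by the 90% rule and not non-inferior at one-sided 0.025.

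**Step 4. How often they disagree.**

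- True difference 0: power is 94.6% with one bound of the 90% interval and 90.1% with one bound of the 95% interval, so the rules disagree in 94.6 − 90.1 = 4.5% of trials.
- True deficit near 0.45 cm: about 13% of trials, roughly the peak.
- True deficit 1 cm: 5.0 − 2.5 = 2.5% of trials.

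**Step 5. Effect of the within-margin wording on any repair.** If the interval must lie inside both limits, the chance of meeting both at a true difference of 0 is about 2 × (one-bound power) − 1.

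- 95% interval: 2 × 0.901 − 1 = 0.80 (simulated 0.804).
- 90% interval: 2 × 0.946 − 1 = 0.89 (simulated 0.893).

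Changing 90% to 95% without touching the two-limit wording would therefore cost about ten points of the planned power.

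**The case against.** The strongest reply is that the 0.025 test governs and Figure 4 only illustrates. The sentence that specifies the primary analysis names one-sided 0.025, two other places agree, and the sample size reproduces only at that level. The 90% figure appears once, as a description of error bars in a figure that is captioned as adapted from a cited source. On this reading the type I error is 2.5% as stated.

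That reading is open, and it rules out the stronger inference that the trial's error rate is simply doubled. The doubling holds only if the interval scheme decides. But the reply does not remove the contradiction. The text attaches a verdict to each scenario according to where the interval lies, does not call the bars illustrative, and does not say that the test overrides them. The source of the figure may explain the 90% level, but it does not reconcile it with this trial's alpha. Nor is this a detail left to an analysis plan, since the protocol itself states two incompatible levels.

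A reader might also infer that the superiority verdict (scenario F) becomes a 5% one-sided test. The documents do not support this. The text says only that F would indicate superiority, not whether its interval lies beyond zero or beyond the margin, and Figure 4 was not available for this check.

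It is also fair to say that the design, the sample size and the data collection are unaffected, and that at the planning assumption the two rules agree in about 95% of trials.

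**Conclusion.** The Statistical analysis section contradicts itself on the level at which non-inferiority is decided, and this should be settled before analysis because it governs the primary conclusion. If the 90% interval scheme is followed, false non-inferiority at a true 1 cm deficit is 5.0% against a stated 2.5%. If the stated test is followed, it is 2.5%. The document does not choose.

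The conflict window of 0.396 to 0.494 cm assumes SD 2.5 cm and 133 evaluable women per group, and it would shift with the observed SD and numbers. The 5.0% against 2.5% depends on neither. The conclusion rests on the written description of Figure 4, which gives both the interval level and the non-inferiority rule.

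**What to change.** 1. In the Statistical analysis section and in Figure 4, replace 90% intervals by two-sided 95% intervals (or a one-sided 97.5% bound).
2. State one directional rule. With the difference in pain reduction taken as single minus four injections, declare non-inferiority if the lower bound of the 95% interval is above −1 cm, whatever the upper bound. A result strongly in favour of the single injection then passes, as it should.
3. Let this rule replace the ±1 cm wording and the requirement that the interval lie inside the shaded margin. Changing the percentage alone would leave power at about 80%.

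The cost is a few sentences and a redrawn figure. No further participants are needed on this account: with the one-bound rule at one-sided 0.025, 133 per group gives 90.1% power, which is how the trial was sized.

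### The assurance that an inconclusive result is unlikely holds near a true difference of zero but not for a true deficit of about 0.4 to 1 cm, and it leans on calling margin-straddling intervals inferior

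*Protocol article*

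**What the plan says.** The Sample size section sets the power: "A sample size of 133 in each group will be required to achieve 90% power to detect non-inferiority using a one-sided, two-sample t-test". Alpha is one-sided 0.025, with a margin of 1 cm. The condition attached to this power is that "the true difference between the means is assumed to be zero (cms". On variability, the section says: "A standard deviation (SD) of ± 2.5 on the VAS was conservatively estimated".

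The Hypothesis section defines the alternative as a difference below 1 cm on the 10 cm VAS. A single injection that is truly somewhat worse, by less than 1 cm, therefore counts as non-inferior.

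The Statistical analysis section then describes the possible outcomes in Figure 4, with 90% confidence intervals. An interval entirely to the left of zero (scenario A) is called inferior, intervals inside the margin (C, D, E) are non-inferior, and F is superiority. Of the remaining outcome it says: "An inconclusive result (scenario B) is unlikely as the sample size is sufficiently powered to provide a result". The zero-difference condition is not repeated there, and no power is given for any other true difference.

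**The concern.** Power is a probability at a stated true difference. The Sample size section gives it at one value, zero, and the Statistical analysis section turns it into a general property of the trial. The chance of clearing the margin falls quickly once the single injection is even slightly weaker, and small deficits inside the margin are what a non-inferiority margin exists to tolerate.

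The stake is how a miss is read. The plan tells readers that the trial will give a result, and it supplies the label inferior for any interval that excludes zero on the worse side. Such an interval can still include differences smaller than 1 cm, which the plan's own hypothesis treats as acceptable. A trial that was only too imprecise to clear the margin could then be reported as having shown inferiority.

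**Working it through.** **Inputs** (Sample size section): SD 2.5 cm, margin 1 cm, one-sided alpha 0.025, 133 per arm, assumed true difference 0. Let *d* be the true deficit of the single injection in cm. Positive means worse, which is the left side of the plan's Figure 4.

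**The plan's own figure.** SE = 2.5 × √(2/133) = 0.3066. By the non-central t with 264 degrees of freedom, power at *d* = 0 is 0.8993 with 132 per arm and 0.9015 with 133. The stated 133 is reproduced.

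**Chance of not showing non-inferiority.** Non-inferiority is missed when the estimate plus the half-width *h* reaches 1 cm. In the normal approximation this is 1 − Φ((1 − d)/SE − 1.96):

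- *d* = 0: 1 − Φ(3.262 − 1.960) = 9.6% (9.9% by t)
- *d* = 0.25: 1 − Φ(2.446 − 1.960) = 31.3%
- *d* = 0.4: 1 − Φ(1.957 − 1.960) = 50.1%
- *d* = 0.5: 1 − Φ(1.631 − 1.960) = 62.9%
- *d* = 0.75: 1 − Φ(0.815 − 1.960) = 87.4%

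The chance passes 20% at about 0.14 cm and 50% at about 0.40 cm. If the single injection is 0.2 cm better, it is 2.5%.

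**Splitting the misses under the plan's labels.** The half-width by t is 0.604 for a 95% interval and 0.506 for a 90% interval. With the text's rule for scenario A, a miss is one of three things:

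- B: the interval includes zero and reaches the margin (estimate between 1 − h and h).
- A, straddling: the interval excludes zero but still straddles 1 cm (estimate above both h and 1 − h, below 1 + h).
- Wholly beyond 1 cm (estimate above 1 + h).

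Results by the t distribution with the SD estimated from the data, rounded to whole percent:

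| True deficit | 95%: miss | 95%: B | 95%: A, straddling | 90%: miss | 90%: B | 90%: A, straddling |
|---|---|---|---|---|---|---|
| 0 | 10 | 7 | 2.5 | 5 | 1 | 5 |
| 0.1 | 17 | 12 | 5 | 10 | 1 | 9 |
| 0.25 | 32 | 19 | 13 | 21 | 2 | 19 |
| 0.4 | 50 | 25 | 25 | 38 | 3 | 35 |
| 0.5 | 63 | 26 | 37 | 51 | 3 | 48 |
| 0.75 | 87 | 19 | 68 | 80 | 2 | 77 |

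An interval wholly beyond 1 cm has a chance below 0.3% (95%) or about 0.7% or less (90%) for deficits up to 0.75 cm. Nearly every miss therefore straddles the margin.

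Hand check at *d* = 0.5. With a 95% interval, 1 − Φ((0.604 − 0.5)/0.3066) = 1 − Φ(0.338) = 37%. With a 90% interval, 1 − Φ((0.506 − 0.5)/0.3066) = 1 − Φ(0.020) = 49%. The table's 48% is lower because, with an estimated SD, some 90% intervals have a half-width below 0.5 and can exclude zero while lying inside the margin. The same variation moves B from 1.6% (SD fixed) to 3%.

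**Sensitivity.** The 50% point is 0.39 cm with about 127.5 per arm (319 less 20%) and 0.45 cm with all 319 analysed. With 90% intervals and 133 per arm it is 0.50 cm (0.49 by t).

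**The case against.** The strongest reply is that the sentence concerns scenario B, not every failure to show non-inferiority. By the section's text, B is an interval that includes zero and crosses the margin. On that reading its probability is at most 26% with 95% intervals, and about 1% (SD treated as known) to 3% (SD estimated) with the 90% intervals that the section names, whatever the true difference. This stands: a reader might infer that scenario B itself is likely, and the text does not support that. Figure 4 is not available here, so how B is drawn cannot be checked. What the reply does not do is vindicate the reason given. With 90% intervals B is rare because the half-width is about half the margin and other misses are moved to scenario A, not because the trial has power at those differences. With 95% intervals, 19% at 0.25 cm and 26% at 0.5 cm are hard to call unlikely.

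A reader might also infer that the assurance holds only at exactly zero, or fails over most of the range called non-inferior. Neither is supported. The chance of a miss is 17% at a 0.1 cm deficit and lower than 10% for any difference favouring the single injection. It exceeds 50% over 60% of deficits from 0 to 1 cm, but over only 30% of the ± 1 cm range that the section gives, and the alternative hypothesis states no lower bound.

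It is also true that the zero-difference assumption is disclosed in the Sample size section, that assuming zero is conventional, and that the sentence sets no test or sample size. Rewording it alone would change no result. The scenario A label is different, because it decides the reported conclusion.

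**Conclusion.** The point holds in a limited form. The assurance is fair at or near a zero difference (about 10% failure) and when the single injection is better. For a true deficit of about 0.4 to 1 cm, still non-inferior under the alternative hypothesis, failure to show non-inferiority is more likely than not with a 95% interval. With 90% intervals that starts at about 0.5 cm.

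The practical consequence lies in the scenario A rule. At a true 0.5 cm deficit, about 37% (95%) to 48% (90%) of trials would be labelled inferior on an interval that straddles the margin.

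This rests on the protocol's SD of 2.5, 133 analysed per arm, and scenario A as worded in the text. A reader might conclude that the sample size is miscalculated; it is not, since 133 per arm is right on its inputs.

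**What to change.** In the Statistical analysis section, make the sentence conditional on a true difference of zero or delete it, and replace the scenario A wording. For example:

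> Power to show non-inferiority is 90% if the true difference is zero. Any confidence interval that includes a 1 cm deficit for the single injection will be reported as non-inferiority not shown. The single injection will be called inferior only if the whole interval lies beyond a 1 cm deficit.

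Giving power at other deficits, about 68% at 0.25 cm and 37% at 0.5 cm (95% interval), would help readers but is optional. The reporting rule works with either interval width. The mismatch between the 90% intervals in this section and the one-sided 0.025 test, which pairs with a 95% interval, needs settling separately.

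The cost is wording only. No extra participants are needed and the analysis is unchanged. The drawbacks are a less favourable stated assurance and that some results the current text would call inferior become non-inferiority not shown.
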